### Study Overview

This protocol is reported in accordance with the SPIRIT (Standard Protocol Items: Recommendations for Interventional Trials) 2025 guidelines for randomized trials, and any significant modifications to the protocol will require prior approval from the study sponsor. An overview of the study design is shown in Figure 1. A total of 210 participants will enroll in this randomized controlled clinical trial with a parallel-group design and equal allocation. All participants will receive a 12-month IDWL program, and those completing the 3-month assessment visit will be randomized to receive (1) a 9-month yoga program (YOGA; delivered during months 4‐12) or (2) a 9-month contact-matched control “Health & Wellness program” (WELLNESS; delivered during months 4‐12). The choice to delay randomization to YOGA or WELLNESS until after the 3-month assessment, rather than at baseline, was made to give participants time to build foundational WL skills without added burden and to reinforce self-regulatory skills at a time (3 months) when WL-related motivation may begin to dip [7,52]. Additional rationale to delay randomization to YOGA or WELLNESS is provided in the discussion. A full description of all intervention components is detailed below and conforms with the TiDieR (Template for Intervention Description and Replication) checklist for intervention reporting to enhance clarity and replicability.

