Yoga and wellness classes will be delivered via videoconferencing software (ie, Health Insurance Portability and Accountability Act [HIPAA]–compliant Zoom; Zoom Video Communications). There will be no intervention during months 13‐18. Randomization will occur at the 3-month assessment (ie, 3 months into the IDWL) in equal numbers based on a permuted block randomization procedure with small, random sized blocks, stratified by biological sex, racial or ethnic minority status, and percent WL achieved during the first 3 months of the WL program (<5% vs ≥5% WL). The randomization scheme was generated by the study statistician using R Studio (version 3.6.0) and uploaded into REDCap directly (to ensure study staff was kept blinded toward the full schematic). Participants will be recruited in cohorts over the study period. Assessments of weight, aerobic PA minutes, dietary lapses, potential lapse triggers (eg, affect, craving, and dietary temptations), and self-regulation mediator variables will be measured at baseline, 3 months (just prior to randomization), 6 months (mid-treatment), 12 months (postintervention), and 18 months (following a 6-month period of no intervention). At each assessment period, data will be collected via a series of REDCap questionnaires, an Actigraph accelerometer, and a 10-day EMA protocol (ie, 5 surveys per day over 10 days with each survey taking 2‐5 minutes to complete).

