### Study Aims

The primary aim of the PATH Trial is to compare the treatment effects of IDWL and YOGA versus IDWL and WELLNESS on weight change at 12 months. The primary weight outcome is absolute weight change from baseline to 12 months. It is hypothesized that WL will be greater in those randomized to the YOGA when compared to WELLNESS.

Secondary aims of this study are (1) to compare YOGA and WELLNESS at 12 months on dietary lapses and potential lapse triggers as assessed via EMA and (2) to examine self-regulation mediators (eg, mindfulness, self-compassion, distress tolerance, self-efficacy, and inhibitory control) of the treatment effect on primary (ie, weight change) and secondary outcomes (ie, dietary lapses) at 12 months.

Exploratory aims are to examine the long-term (18 months) effects of yoga on primary and secondary outcomes, to explore potential moderators (3-month WL, race or ethnicity, biological sex, and BMI) of the treatment effect on weight change, and to explore the effect of yoga on participation in aerobic exercise.

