### Questionnaire Measures

At each assessment, a series of questionnaires will be completed via REDCap. At baseline only, demographic information and food insufficiency will be assessed. Questionnaire measures of self-regulatory mechanisms are found in Table 3 and will be completed at all assessment time points by all participants. At follow-up time points, program satisfaction questionnaires will also be completed, which will be used to assess the acceptability of the IDWL, yoga, and wellness programs. Yoga participants will also be asked to complete several additional questionnaires at follow-up related to their perception of the yoga classes, perceived benefits of practicing yoga [59], and frequency and duration of yoga practice.

**Table 3. T3:** Validated questionnaires administered at baseline, 3-month, 6-month, and 18-month assessments to assess various aspects of self-regulation.

Questionnaire	Assessment	Scoring
Weight Control Strategies [60]	Self-monitoring, exercise, and diet as weight control strategies	0‐90; comprised of a 30-item scale with four component solution for the subscales: (1) dietary choices, (2) self-monitoring strategies, (3) physical activity, and (4) psychological coping
Five Facet Mindfulness Questionnaire [61,62]	Mindfulness (including one’s ability to observe, describe, and act with awareness, and be nonjudgmental and nonreactive to one’s inner experience)	Comprised of 5 subscales: nonjudging (8-40), nonreactivity (7-35), observing (8-40), describing (8-40), and acting with awareness (8-40)
Distress Tolerance Scale [63]	Perceived capacity to tolerate distress	15‐75; higher scores indicate greater distress tolerance
Self-Compassion Scale [64]	Degree to which individuals act compassionate toward themselves when experiencing a difficult time	26‐130; higher scores reflect higher levels of self-compassion
Weight Efficacy Lifestyle Questionnaire [65]	Self-efficacy (one’s confidence in their ability to avoid overeating when faced with certain situations)	20‐100; higher scores indicate greater self-efficacy in managing weight-related behaviors
Behavioral Inhibition System (BIS) and Behavioral Activation System (BAS) [66]	Inhibitory control (measures motivation to avoid aversive outcomes)	BIS: 7‐28; higher BIS scores indicate greater sensitivity to punishment and BAS: 4‐16; higher BAS scores indicate greater sensitivity to reward

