#### Primary Aim

We will examine treatment effects on weight change from baseline to 18 months using a longitudinal mixed effects regression model. Absolute weight will be regressed on treatment assigned (YOGA vs WELLNESS), initial WL (from baseline to 3 months), and identified confounders. Model estimates and group comparisons will be generated for the 12-month primary end point, with contrasts specified to allow for understanding group differences in the postrandomization period (eg, 3‐12 months controlling for baseline to 3 months). Models will include a participant-specific intercept and random slope terms to adjust for repeated measurements within participants over time. Further, we will test for clustering by cohort and adjust, if needed. Mixed models are flexible, in that they allow for a wide range of specifications of the time effect (linear and nonlinear), which is particularly important in WL data, where outcomes do not necessarily follow a linear pattern over time.

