#### Secondary Aims

Using a similar analytic approach as that described for the primary aim, we will examine intervention effects on secondary outcomes, including frequency of dietary lapses and potential lapse triggers (eg, affect, cravings, and ability to resist dietary temptations), as assessed via EMA. Namely, longitudinal mixed effects models will be specified that regress outcomes over time on intervention group (YOGA vs WELLNESS), time, intervention*time, baseline value of the outcome, and confounders. Models will also adjust for the clustering of data within participants. Effects of day and measurement period will be tested, and adjustments made, as needed.

To evaluate the secondary aims of this study, we will examine potential mediators (eg, affect, mindfulness, self-compassion, and distress tolerance) of the treatment effect on primary (ie, weight change) and secondary outcomes (ie, dietary lapses) using a multiple mediator model with bootstrapped SEs (10,000 bootstrapped samples). Models estimate the path coefficients (a path: effects of YOGA vs WELLNESS on changes from baseline in potential mediators and b path: effects of changes from baseline in potential mediators on WL or lapse outcomes) as well as the indirect effect of intervention (ab path: YOGA vs WELLNESS on outcomes through the mediators).

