This design was chosen as the best method of answering the questions central to the study. For example, the use of an equal contact-time wellness program for the control arm, delivered through the same live, synchronous videoconferencing modality as yoga, provides a stringent test of the relative efficacy of yoga as a complementary therapy to IDWL. The decision to implement yoga at the start of week 14, rather than week 1, was made so that participants can dedicate their focus to initiating important WL skills and achieving program goals at the start of the program (eg, regular self-weighing, self-monitoring, calorie restriction, and aerobic exercise). Adding yoga at week 1 would further increase participant burden, which is already high at this time. Delaying yoga until week 14 allows additional time for these important WL skills to become more routine, which then allows individuals more time to dedicate to practicing yoga. Further, given that maximal WL in IDWL programs is achieved around 3 months [7,52] (earlier than what is observed with in-person treatment [35]), one way to bolster WL at this time would be to add an intervention component, which can both add novelty and strengthen self-regulation. Research supports this approach, as individuals report that over time, boredom increases; it requires more effort to stay on track, and the cost-benefit ratio for WL increases (ie, the effort required to adhere to WL practices is greater than the positive feedback received for adherence) [35,70-74]. This makes continued diligence to self-regulatory WL behaviors challenging, particularly during times of high stress, emotional difficulties, or when exposed to highly palatable foods. Our pilot study, which also implemented yoga following a period of WL treatment, provided further support for this decision [51].

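### The mediation paths use mediator changes from month 0, three months before randomisation, so a response shared with the outcome before yoga starts can be reported as mediation

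*Protocol article*

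**What the plan says.** - **Mediator metric.** Secondary Aims puts the a path on mediator changes from baseline and describes the b path as "effects of changes from baseline in potential mediators on WL or lapse outcomes".
- **Outcome metric.** Study Aims: "The primary weight outcome is absolute weight change from baseline to 12 months". The second mediation outcome is dietary lapses.
- **Timing.** Study Overview: "All participants will receive a 12-month IDWL program, and those completing the 3-month assessment visit will be randomized". The month-3 assessment is a separate visit, "3 months (just prior to randomization". Yoga and wellness classes run only in months 4 to 12.
- **Early response.** The Discussion (Principal Findings) says that "maximal WL in IDWL programs is achieved around 3 months".
- **Adjustment.** The Primary Aim model for weight includes "initial WL (from baseline to 3 months), and identified confounders" and specifies a contrast for the period after randomisation. The mediation paragraph names no month-3 term. The lapse models adjust for the baseline value of the outcome.
- **Inference.** Indirect effects are estimated "using a multiple mediator model with bootstrapped SEs (10,000 bootstrapped samples"). No test or interval type is named.
- **Measurement.** The Table 3 heading reads "Validated questionnaires administered at baseline, 3-month, 6-month, and 18-month assessments", without month 12. The text of Questionnaire Measures and the Outcome Measures overview both include month 12.

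**The concern.** A change from month 0 has two parts: the response to the common program in months 0 to 3, and the change after randomisation. Only the second can carry an effect of yoga. People who do well on the common program may both improve on, say, self-efficacy and lose weight, so the first parts of the two change scores are likely to be related. The regression of outcome change on mediator change absorbs that relation and reports it as b. Multiplied by a genuine a path, it gives an indirect effect that yoga did not produce.

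Mediation is a stated secondary aim, the sample was enlarged partly to serve it, and the Discussion presents these pathways as a distinctive contribution of the trial. The pilot results and the hypotheses expect yoga to shift the mediators, so the anticipated scenario is the one in which the artefact matters.

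**Working it through.** **No plan figure to reproduce.** The article gives no effect size or power for mediation. The check therefore asks how the stated metric behaves when the true b is zero.

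**Inputs from the article.** Total 210; attrition below 20%. At 20%, 210 × 0.8 = 168 completers, 84 per arm.

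**Assumptions, not in the article.** One mediator. Changes before and after randomisation each have SD 1. The two periods are independent of each other. Yoga shifts the later mediator change by a = 0.5. True b = 0. The month 0–3 changes in mediator and outcome have correlation ρ = 0.2, 0.3 or 0.5. Two-sided 5% level.

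**Step 1, bias in b.** Within arm, mediator change from month 0 has variance 1 + 1 = 2, and its covariance with outcome change is ρ. The expected b is therefore ρ/2: 0.10, 0.15 and 0.25, where the truth is 0.

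**Step 2, rejection of b.** SE(b) ≈ √[(2 − ρ²/2)/(168 × 2)] = 0.077, 0.076 and 0.075. The rejection probability is Φ(b/SE − 1.96): about 26%, 50% and 92%. Simulation gave 26%, 51% and 92%.

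**Step 3, rejection of a.** SE(a) = √2 × 2/√168 = 0.218, so z = 0.5/0.218 = 2.29 and power is Φ(0.33) ≈ 63%.

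**Step 4, both paths.** Multiplying steps 2 and 3 gives about 16%, 32% and 58%, a rough guide to the false rate for the indirect effect. Simulated rates for the product, weight outcome:

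| Analysis | ρ = 0.2 | ρ = 0.3 | ρ = 0.5 |
|---|---|---|---|
| Change from month 0, percentile-type limits | about 15% | about 28% | about 55% |
| Change from month 0, product divided by SE | about 5% | about 10% | about 35% |
| Month-3 mediator and outcome terms added | about 6% or less | about 6% or less | about 6% or less |

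**Step 5, boundary cases.** At ρ = 0 the product was rejected in about 3% of trials with percentile limits, so there is no inflation. With a = 0 and ρ = 0.3, b was rejected in 50% of trials but the product in only 2.3% (percentile) or 0.5% (product/SE).

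**Step 6, does the primary model's covariate suffice?** Weight change minus initial weight loss leaves only the later change, so b returns to about 0 (rejected in 4% to 6% of trials). For lapses, the covariate removes only the part of the early lapse response that is shared with early weight loss. With all pairs of early changes correlated at ρ, the expected b is ρ(1 − ρ)/(2 − ρ²):

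- ρ = 0.2: 0.16/1.96 = 0.08
- ρ = 0.3: 0.21/1.91 = 0.11
- ρ = 0.5: 0.25/1.75 = 0.14

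The simulated false indirect-effect rate for lapses stays at about 10%, 17% and 30% with percentile-type limits. Month-3 mediator and lapse terms bring it to about 5% or less.

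**Step 7, choice of test.** With no bias present and 168 completers, power for the product (percentile versus product/SE) was 35% vs 15% (a 0.3, b 0.2), 50% vs 26% (0.39, 0.2), 70% vs 51% (0.39, 0.3), 87% vs 74% (0.5, 0.3) and 90% vs 82% (0.5, 0.39). The gap is 8 to 24 points.

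**The case against.** **The adjustment is unstated, not excluded.** An article condenses, and the Primary Aim model already carries initial weight loss and a contrast for the period after randomisation. If the mediation model inherits that covariate, the weight analysis is largely repaired. This stands for weight. It does not reach lapses (step 6). Nor is the change metric an omission: the paragraph states it outright.

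**The size is conditional.** The article gives no correlation between the early changes; at zero there is no artefact. The a path is randomised and unbiased, so a false indirect effect also needs a real yoga effect on the mediator. This stands, and the rates above are scenarios, not predictions.

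**Stronger readings that the article does not support.**
- A reader might infer that the product will be tested against a normal cut-off and so lose power. The article mentions bootstrapped standard errors but names no test, and the same resamples give percentile limits. The larger false-positive rates and the power loss also belong to different tests, so they cannot both apply in full.
- A reader might infer that mediator and outcome are taken together at month 12, leaving direction unclear. The stated 12-month time point attaches naturally to the treatment effect on the outcomes, and no mediator visit is fixed.
- A reader might infer from the Table 3 heading that no 12-month questionnaire is given. Two text passages say otherwise, so this is a caption slip.

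**Conclusion.** The point holds as a badly chosen metric in a secondary analysis. Mediator and weight changes from month 0 both contain the response to the common program before randomisation, and the mediation paragraph does nothing to separate it. The same problem applies to lapses if they are analysed as change from month 0, or adjusted only for their month-0 value.

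Under the working assumptions, false mediation is reported in about 15%, 28% and 55% of trials (percentile-type limits), or 5%, 10% and 35% (product/SE), for early-change correlations of 0.2, 0.3 and 0.5. These figures rest on an assumed correlation, an assumed yoga effect of 0.5 SD on a single mediator, equal variances, and independence of the early and later changes. It does not follow that the trial will report false mediation. The primary comparison of weight between arms is unaffected. The test for the indirect effect needs clarifying, and the Table 3 heading is editorial.

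**What to change.** 1. In Secondary Aims, replace mediator change from baseline with the mediator value after randomisation, adjusted for its month-3 value.
2. Adjust the outcome model for the month-3 mediator and for the month-3 and baseline values of the outcome, for lapses as well as weight.
3. State that indirect effects are judged by percentile confidence intervals from the planned 10,000 bootstrap samples.
4. Optionally, add an analysis with the 6-month mediator as a sensitivity check on temporal order. It misses mediator change after month 6 while yoga continues to month 12, so it should not replace the main analysis.
5. Bring the Table 3 heading into line with the text on the 12-month questionnaires.

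The cost is analysis wording and a few extra covariates. The month-3 measurements of mediators, weight and lapses are already scheduled, so no new data collection is needed.

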#### Exploratory Aims

To examine longer-term treatment effects on weight change, we will generate model estimates and perform group comparisons for the 18-month end point using the mixed effects model of weight described earlier (aim 1). We will also examine moderators of the treatment effect on weight change from baseline to 12-month follow-up, including initial WL (weight change from baseline to 3 months), baseline BMI, race or ethnicity, and biological sex, using a similar analytic approach to that described in the primary aim.

#### Missing Data

Analyses will be on the intent-to-treat sample (everyone randomized will be included in the final analysis) under various assumptions about the missing data mechanism. Sensitivity to these assumptions will be tested. Specifically, we will gather follow-up information and reasons for dropout regardless of protocol completion and censor at the point of loss. We will compare the robustness of our findings using 3 statistical approaches for handling missing data. First, we will use a multiple imputation approach to impute missing outcomes. Next, we will use inverse probability weighting with propensity scores. This is a two-step method: (1) using logistic regression, the probability of missingness is modeled as a function of baseline covariates and baseline values of the outcome and (2) the inverse of the propensity scores (predicted probabilities of dropout from the first step) serves as weights in our regression model of the outcomes. Provided the data are missing at random or that the probability of missingness can be fully explained by observable data, this approach produces asymptotically unbiased estimates. To allow for the possibility that the missing at random assumption may not hold, we will also use a third approach, pattern mixture models, in which the distribution of the outcome is assumed to follow a mixture of 2 distributions: one for those who complete follow-up and another for those who do not.

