### Internet-Based WL Program

All participants will receive a 12-month, fully automated IDWL program, which has been used in previous trials [7,54,55]. Prior to the start of the program, participants will be asked to watch a brief video, which will provide them with the basics for navigating the study website. The goal of the program is to induce a 1‐2 lb (~0.5‐1 kg) WL per week. To assist in achieving this goal, individuals will be given an initial daily calorie intake goal of 1200‐1800 kcal per day depending upon starting weight. Participants will also be taught to increase or decrease calorie intake as necessary based on WL progress and goals. There will be also a moderate-intensity aerobic exercise (eg, walking, cycling, and elliptical) goal, which progresses to 150 minutes per week. Participants will be instructed to self-monitor body weight, energy intake, and PA daily over the 12-month WL period, as self-monitoring in a behavioral WL program has been shown to be associated with weight change [56]. They will be provided with a smart scale, which will allow for wireless [57] transmission of weight data to the study website. Participants will be given the option to track their calories and exercise minutes in the Fitbit mobile app, in which case data will automatically transfer to the study website through an application programming interface built specifically for this study. However, if they use a different tracking method, they will be asked to manually input their daily calorie intake and exercise minute totals on the study website. Computer-generated, personalized feedback will be provided using these self-report data. Participants will also be instructed to view 10‐ to 15-minute multimedia lessons, which are modeled after the Look AHEAD Trial [57]. Example lesson topics including strategies for increasing PA, eating out at restaurants, and problem-solving. Video lessons and automated feedback are provided weekly during the first 3 months of the IDWL program and monthly during months 4‐12. Participants also have access to healthy recipes and tip sheets (eg, meal planning strategies, eating healthy on a budget, and exercising safely) via the study website. During months 4‐12, automated text messages, which are informational and motivational in nature, will also be sent to participants twice per month and will differ between yoga and wellness conditions.

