### Adherence Measures

Intervention adherence will include the percentage of IDWL lessons viewed and frequency of self-monitoring energy intake, weight, and aerobic exercise minutes entered into the study website (or transmitted to the study website via the Fitbit app) by participants over the study duration. Attendance at live yoga and wellness classes will also be assessed. Additional adherence metrics in the yoga condition include the number of times each prerecorded yoga video was viewed and weekly minutes per week of yoga practice (reported on the study website). During months 13‐18, self-reported yoga practice will be assessed via monthly surveys.

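### The inverse-probability-weighting analysis models dropout on baseline data alone, although 3-month, 6-month and smart-scale weights will be available to it

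*Protocol article*

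**What the plan says.** The Missing Data section plans three approaches whose results are to be compared: multiple imputation, inverse probability weighting and pattern mixture models. For the weighting it names the covariates: "using logistic regression, the probability of missingness is modeled as a function of baseline covariates and baseline values of the outcome". It gives the condition under which the result is asymptotically unbiased: "Provided the data are missing at random or that the probability of missingness can be fully explained by observable data". For the imputation it names no variables: "First, we will use a multiple imputation approach to impute missing outcomes".

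The trial will hold much more than baseline data. Apart from baseline, the assessments are at "3 months (just prior to randomization), 6 months (mid-treatment), 12 months (postintervention), and 18 months" (Study Overview). Only people who complete the 3-month visit are randomised, so everyone in the analysis has reached that visit. Loss over the first 3 months is also a stratification factor (Study Overview) and a covariate of the primary model (Primary Aim).

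Between visits, "Participants will be instructed to self-monitor body weight, energy intake, and PA daily over the 12-month WL period", and "They will be provided with a smart scale, which will allow for wireless [57] transmission of weight data to the study website" (both Internet-Based WL Program). The use stated for these self-monitored data is as an adherence measure: "frequency of self-monitoring energy intake, weight, and aerobic exercise minutes entered into the study website" (Adherence Measures). Attendance at live classes is recorded as well.

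**The concern.** Weighting removes dropout bias only to the extent that the covariates in the dropout model explain dropout. Here those covariates were all measured 3 months before randomisation. They cannot reflect how a participant's weight moved afterwards, whether the participant stopped weighing or attending, or which programme was assigned.

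The article itself gives reason to think that later events matter: it expects motivation to dip around 3 months and effort to grow over time (Study Overview; Principal Findings), and from month 4 the arms attend different classes. If people leave because of what happens after baseline, the weighted estimate will sit close to the unweighted complete-case estimate. A reader could then take agreement between the two as evidence of robustness when the weights have corrected nothing.

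The covariates are stated, so this is a choice that has been made and not a detail left to an analysis plan.

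**Working it through.** **1. Inputs.** From the article: 210 participants, equal allocation, attrition below 20% at end of treatment, the assessment schedule and the dropout covariates above. The article gives no figure for this point that could be reproduced.

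**2. The condition.** Let R = 1 if the 12-month weight is observed and X the covariates in the dropout model. Weighting by 1/P(R = 1 | X) is consistent if, given X, R does not depend on the 12-month weight. The article states the condition in terms of all observable data, but its X is baseline only. The two agree only if dropout, given baseline, is unrelated to later weight change.

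**3. Size of the bias.** Simulation of 600,000 participants per scenario, about 20% missing at 12 months. All of the following are assumptions:
- Baseline weight 95 kg (SD 14); 3-month change -4 kg (SD 3.5).
- SDs of later increments: 2.5 kg (months 3 to 6), 3 kg (6 to 11), 1.0 kg (11 to 12).
- True difference -2.0 kg, of which 40% accrues by month 6, 55% by month 11 and 5% in the last month.
- Log-odds of dropout per kg of poorer change to month 11. Same slope in both arms: 0.3 x 0.5/1.5 = 0.10 and 0.6 x 0.5/1.5 = 0.20. One arm only (yoga): 0.3 x 0.6 = 0.18 and 0.6 x 0.6 = 0.36, with 0 in the other arm.

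The outcome model contained arm, baseline weight and 3-month change. The baseline-only dropout model was given arm and the arm-by-baseline product as well, which is more than the article states. Estimated difference (kg):

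| Dropout depends on | Complete cases | Weighted, baseline only | Weighted, + 3 and 6 months | Weighted, + late scale weight |
|---|---|---|---|---|
| Baseline weight only | -1.98 | -1.98 | -1.98 | -1.99 |
| Recent change, both arms, 0.10 | -1.97 | -1.97 | -1.99 | -2.00 |
| Recent change, both arms, 0.20 | -1.87 | -1.87 | -1.91 | -2.00 |
| Recent change, one arm, 0.18 | -2.51 | -2.51 | -2.32 | -2.01 |
| Recent change, one arm, 0.36 | -2.87 | -2.87 | -2.61 | -2.00 |

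In every row, baseline-only weighting equals complete cases to two decimals. Against -2.0 its bias is 0.03 and 0.13 kg (both arms) and 0.51 and 0.87 kg (one arm). The one-arm slopes are also steeper per kg, so the contrast between the two settings is not due to the arm difference alone.

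The reason is visible in the share of variance of 12-month change explained: about 3% by baseline weight and arm, 66% after adding the 3- and 6-month weights, and 97% after adding a scale weight one month earlier. The last column is a best case, because every simulated participant has an error-free month-11 weight. For people who stop weighing earlier, the gain would be expected to lie between the last two columns.

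**4. Precision.** With 20% missing, 210 x 0.8 = 168 weights are observed. If 25%, 50% or 75% of the missing weights could be recovered (assumed shares), n = 210 x (0.8 + 0.2 x share) = 178.5, 189 or 199.5. Against a complete-case analysis, the SE ratio sqrt(168/n) is 0.970, 0.943 or 0.918, a gain of 3%, 6% or 8%. But the planned mixed model already borrows from earlier weights. Its variance is roughly proportional to (1 - R2 x f)/n, with f the fraction still missing. With the assumed R2 = 0.66:
- No recovery: (1 - 0.66 x 0.20)/168 = 0.005167
- 25%: (1 - 0.66 x 0.15)/178.5 = 0.005048, SE down 1.2%
- 50%: (1 - 0.66 x 0.10)/189 = 0.004942, SE down 2.2%
- 75%: (1 - 0.66 x 0.05)/199.5 = 0.004847, SE down 3.1%

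**The case against.** The strongest reply is that weighting is one of three sensitivity approaches and that the primary analysis does not depend on it. The mixed model contains arm, initial weight loss and the repeated scheduled weights, so it uses the 3- and 6-month data of people lost before month 12. This stands, and it limits the point to the weighting analysis.

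A reader might infer that the plan as a whole throws the scale data away. The document does not support that. The imputation variables are not stated, which is different from being stated to exclude scale weights, and an article may leave such lists to a fuller document.

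A reader might also infer that usable weights will keep arriving from people who miss the 12-month visit. The article says only that participants are told to weigh daily and that the scale can transmit. Assessment weights are also taken at home on mailed smart scales, so someone still weighing near month 12 is likely to be captured anyway, and those who disengage may stop weighing. The amount recoverable is unknown.

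A precision gain of 3% to 8% would likewise be too strong, because it presumes a complete-case comparison that is not planned.

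Finally, the simulation did not run the planned mixed model, multiple imputation or pattern mixture model, and its larger biases arise only when dropout follows weight change in one arm. This too stands: it shows what baseline-only weighting can miss, not the bias of the trial's primary result.

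Reading baseline as including the 3-month visit does not rescue the model, because the article lists the two as separate assessments.

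**Conclusion.** The point holds for the weighting analysis. As stated, its dropout model meets the article's own condition only if dropout depends on baseline alone, and it omits even the 3-month weight, which the design and the primary model both treat as important.

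If dropout follows later weight change, the uncorrected bias is about 0.03 to 0.13 kg with equal slopes in the arms and about 0.5 to 0.9 kg if it occurs in one arm only, on an assumed 2.0 kg effect; it is essentially nil if dropout depends on baseline alone. These sizes rest on assumed SDs, slopes and about 20% missing, which is the upper end of the attrition the article expects. The SE gain would be about 1% to 3% under the assumed R2 of 66%, so bias and not precision is the reason to act. The primary mixed model is not called into question by this point.

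**What to change.** In the Missing Data section:

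- Model missingness on arm, baseline covariates, the 3- and 6-month weights, the last transmitted scale weights before loss, weighing frequency and class attendance.
- Use the same auxiliary variables in the multiple imputation, and say so.
- State how scale weights transmitted after a participant's last completed visit are handled, since the section also speaks of censoring when a participant is lost.
- Prespecify a plausibility filter and an indicator for having no recent scale weight. Weights taken outside the assessments are noisier, may come from another household member and may stop at disengagement.

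Optionally, add a sensitivity analysis in which transmitted weights from a prespecified window ending at the 12-month visit enter the imputation as predictors. They should not simply replace the missing weight, because that would mix measurement procedures and ignore uncertainty. A window running past the visit would include time after the daily-weighing instruction and the intervention have ended.

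The cost is analysis programming and the filter; no new data are collected. Because staff are not blinded to assignment, the variables and the window should be fixed before outcomes by arm are examined. Enrolment was still open when the article was written.
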